### Outcome assessment and follow-up

4.3

This study employs a rigorous and comprehensive assessment schedule, as outlined in Table 2, to evaluate a broad spectrum of outcomes across different time intervals: at 6 months (Trial Completion), 12 months (First Follow-up), and 18 months (Second Follow-up) (detail shown in Table 2).

**Table 2 tab2:** Schedule of assessments and follow-up intervals for study period.

Assessments	Study period		
	Trial Completion (6 months)	Follow-up (12 months)	Follow-up (18 months)
MoCA (30) and MMSE (31)	✓		✓
IADL (32)	✓		
Subjective memory complaints (33)		✓	
Descriptors	✓		✓
Rey-0 complex figure, Judgement of line orientation, prospective memory, spatial memory, Kirby delay discounting	✓		
Physical performance	✓		
Short physical performance battery	✓		✓
400 m walk test	✓		
30 s sit-to-stand	✓		✓
Reproductive, Florida cognitive activitylifetime stimulation, and epic-Norfolk physical activity questionnaire (34)	✓		
FCl, PSOl, and life space questionnaire (35)	✓	✓	✓
State and trait anxiety inventory	✓		✓
Health related quality of life and sedentary behavior	✓	✓	✓

**Cognitive assessments**: the MoCA (Montreal Cognitive Assessment) and MMSE (Mini-Mental State Examination) are conducted at the trial completion (6 months) and again at the 18 months follow-up. These tools are essential for measuring cognitive function and detecting any changes over time.

**Functional and physical assessments**: the study includes the Instrumental Activities of Daily Living (IADL) assessment at the 6 months mark to evaluate functional abilities. Physical performance is measured at 6 months using tests such as the Short Physical Performance Battery, the 400 m Walk Test, and the 30 s sit-to-stand test. These assessments are repeated at the 18 months follow-up to track physical endurance and mobility changes.

**Memory and psychological assessments**: subjective memory complaints are evaluated at the 12 months follow-up, while other detailed memory tests like the Rey-O Complex Figure and Judgement of Line Orientation are conducted at 6 months. The State and Trait Anxiety Inventory is administered at both the 6 months and 18 months follow-ups to assess changes in anxiety levels.

**Lifestyle and quality of life questionnaires**: the study also incorporates the Reproductive, Florida Cognitive Activity Lifetime Stimulation, and Epic-Norfolk Physical Activity Questionnaire at the 6 months mark. In addition, the FCI (Frailty Criteria Index), PSQI (Pittsburgh Sleep Quality Index), and Life Space Questionnaire are administered at all three assessment points (6, 12, and 18 months) to monitor lifestyle changes and quality of life.

**Health-related assessments**: health-related quality of life and sedentary behavior are evaluated at all three time points to provide a comprehensive view of the participants’ overall health status and lifestyle habits.

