**Objective:**

This study aims to develop and evaluate a multimodal data-driven AI system for personalized exercise prescriptions, targeting individuals with mental illnesses. By leveraging AI, the study seeks to overcome the limitations of conventional exercise regimens and improve adherence and mental health outcomes.

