### Study design

2.1

In the first phase, we focus on developing a multimodal data-driven intelligent system for exercise prescription. To achieve this, we will initially recruit 1,000 participants for AI model training and testing. Of these, 80% (800 participants) form the training set. To enhance the robustness and generalizability of the AI model, we will use ChatGPT to simulate an additional 9,200 cases based on the initial 800, resulting in a comprehensive training set of 10,000 instances. The remaining 20% (200 participants) will be reserved as a testing set. This diverse dataset will then be annotated by a team of 10 experienced doctors from the Department of Mental Health at Guangdong Second Provincial General Hospital. Their expertise will ensures the accuracy and clinical relevance of the data labeling, which is critical for the development of a reliable and effective AI system.

In our analysis, we will set the effect size at 0.5 to assess the intervention’s effectiveness. This value represents a medium effect size, which is considered substantial in the context of our study. Following the development and preliminary testing of the AI model, the second phase of the study will involves an RCT with 50 participants. These participants are randomly divided into two groups: 25 in the experimental group and 25 in the control group. The experimental group will receives personalized exercise prescriptions generated by the newly developed AI system, while the control group will receives standard exercise recommendations. This phase aims to evaluate the efficacy of the AI-driven exercise prescription system in a real-world clinical setting. The RCT’s design ensures that the results are robust and can be attributed specifically to the intervention, thereby providing strong evidence of the system’s potential benefits for individuals with mental illnesses.

The effectiveness of the AI-driven exercise prescriptions is evaluated at multiple time points: initially at the end of the 6 months trial period (Trial Completion Assessment), followed by a 6 months follow-up assessment and a 12 months follow-up assessment. These assessments are designed to track and compare the short-term and long-term impacts of the AI-driven exercise prescriptions on the mental health outcomes of the participants (shown in Figure 1).

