Health care resource utilization (HRU) (42)	A 10-item questionnaire that asks participants about their health care visits, services used, and their ability to perform chores, aimed at calculating the economic burden of health care needs
State and trait anxiety inventory (STAI) (43)	This comprehensive 40-item questionnaire evaluates mood and levels of anxiety, providing valuable insights into the psychological well-being of participants
Center for epidemiologic studies depression scale (44)	A detailed 20-item questionnaire designed to measure symptoms associated with depression, focusing on experiences over the past week
Pittsburgh sleep quality index (PSQI) (45)	An in-depth 19-item questionnaire that assesses sleep quality over the previous month. It employs subjective ratings across seven different components, including sleep quality, latency, duration, habitual efficiency, disturbances, use of sleeping medication, and daytime dysfunction
STOP bang questionnaire (46)	An 8-item tool aimed at assessing the risk of obstructive sleep apnea, crucial for understanding sleep-related health risks
Life space questionnaire (47)	A 6-item questionnaire that measures the mobility extent of older adults, providing insights into their functional range and independence
Everyday memory questionnaire (EMQ) (48)	A comprehensive 28-item questionnaire that evaluates memory failures occurring in the past 3 months, offering a window into cognitive health

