### Statistical analysis

4.5

In the initial phase of our statistical analysis, we will employ descriptive statistics to summarize the participant characteristics, including demographics, baseline health measures, and other relevant variables. This step will involve calculating means, standard deviations, and proportions to provide a clear overview of the study population. Following this, comparative analyses between the intervention and control groups will be conducted using independent *t*-tests (or Mann–Whitney U tests for non-normally distributed data) for continuous variables, and Chi-square tests (or Fisher’s exact tests) for categorical variables. This will enable us to detect any significant differences arising from the intervention.

Considering the multiple assessment points in our study, longitudinal data analysis techniques will be crucial. These methods, including repeated measures ANOVA or mixed-model ANOVAs, will allow us to track and analyze changes over time both within and between participant groups. This approach is essential for understanding the dynamics of the intervention’s impact, accounting for both individual variations and time-dependent factors.

To quantify the intervention’s effectiveness, we will calculate effect sizes, providing a measure of the practical significance of our findings. The handling of missing data, a common challenge in longitudinal studies, will be addressed through methods like multiple imputation or last observation carried forward, ensuring the robustness of our results. All statistical tests will be two-tailed, with a significance level set at *p* < 0.05. We plan to use sophisticated statistical software such as SPSS or R for these analyses, enabling us to apply the most appropriate and advanced statistical techniques for our data.

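### The outcome schedule has no measure of adherence (a stated aim) and no depression scale, and no outcome or visit is primary among about 20 to 35 tests, each at p < 0.05

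*Protocol article*

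**What the plan says.** The Abstract (Objective) states that "the study seeks to overcome the limitations of conventional exercise regimens and improve adherence and mental health outcomes". The Abstract's expected outcomes and the Discussion also name adherence as something the system should improve.

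Section 4.3 and Table 2 give the trial's assessments at 6, 12 and 18 months, intended "to evaluate a broad spectrum of outcomes across different time intervals". The rows cover cognition, daily function, physical performance, memory, lifestyle questionnaires, frailty, sleep, life space, anxiety (STAI), quality of life and sedentary behaviour. There is no baseline column. Neither the table nor its text marks an outcome or visit as primary.

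The CES-D is in Table 1 (section 3.1), described as "A detailed 20-item questionnaire designed to measure symptoms associated with depression". Its role there is as an input to the machine learning model. It is not in Table 2.

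Section 4.5 foresees t-tests or Mann–Whitney tests between groups for continuous variables, and also repeated-measures or mixed ANOVA. It does not say whether the second replaces or adds to the first. On error control it says only this: "All statistical tests will be two-tailed", "with a significance level set at *p* < 0.05".

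Section 2.1 states "we will set the effect size at 0.5 to assess the intervention’s effectiveness", without tying that effect size to an outcome, and allocates "25 in the experimental group and 25 in the control group".

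**The concern.** Two faults compound each other.

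First, the schedule does not match the question. Adherence is a named aim with no scheduled measure. Depression is the first diagnosis listed in the inclusion criteria (section 2.4) and the worked example for the intervention (section 4.2), but depressive symptoms are not a scheduled outcome. Data not collected during the trial cannot be recovered by any later analysis plan.

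Second, nothing in the document says which result decides the trial. With many instruments, up to three visits, a uniform 0.05 and no ranking, any one significant comparison could be presented as evidence of efficacy, including one on cognition or mobility that is remote from the objective.

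**Working it through.** **Step 1. Aim against schedule**

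| Target | Where stated | In Table 2? |
|---|---|---|
| Adherence | Abstract (Objective, Expected outcomes); Discussion | No. The nearest items are the EPIC-Norfolk activity questionnaire (6 months) and sedentary behaviour (all visits). Both record general activity, not sessions done against sessions prescribed. |
| Mental health: anxiety | Eligible diagnosis (2.4) | Yes: STAI at 6 and 18 months |
| Mental health: depressive symptoms | First eligible diagnosis listed (2.4) | No. CES-D is a model input only (Table 1). |

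Section 4.2 gives the intervention as 4 weeks, while section 2.1 speaks of a 6-month trial period. Those statements must be reconciled. If the 4 weeks apply, none of the Table 2 visits falls within the intervention.

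**Step 2. Number of comparisons**

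The document gives no count, so there is no figure of its own to reproduce. Counting instrument by visit from Table 2:

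- MoCA and MMSE: 2 × 2 = 4
- IADL 1; subjective memory complaints 1
- Rey-O, line orientation, prospective memory, spatial memory, delay discounting: 5
- Short Physical Performance Battery 2; 400 m walk 1; sit-to-stand 2
- FCI, PSQI, Life Space: 3 × 3 = 9
- STAI state and trait: 2 × 2 = 4
- Quality of life and sedentary behaviour: 2 × 3 = 6

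Total: 4 + 1 + 1 + 5 + 2 + 1 + 2 + 9 + 4 + 6 = 35, from 19 measures. This leaves out Descriptors, the generic physical performance row, and the row holding the reproductive, Florida and EPIC-Norfolk questionnaires.

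A second count takes the STAI as one score (2 cells, not 4) and adds Florida and EPIC-Norfolk (1 each). It again gives 35, from 20 measures. Counting every named item, with the STAI as one, gives 39. The text of section 4.3 says the physical tests are repeated at 18 months, but Table 2 ticks the 400 m walk at 6 months only; following the text would add one.

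**Step 3. False-positive chances if there is no true effect**

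For K independent tests at two-sided 0.05:

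- at least one significant difference in either direction: 1 − 0.95^K
- at least one favouring the AI arm: 1 − 0.975^K

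| K | Reading of section 4.5 | Any | Favouring AI |
|---|---|---|---|
| 39 | per visit, all named items | 86% | 63% |
| 35 | per visit | 83% | 59% |
| 20 | one longitudinal test per measure | 64% | 40% |
| 19 | one longitudinal test per measure | 62% | 38% |
| 1 | single primary | 5% | 2.5% |

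Expected false positives at K = 35: 35 × 0.05 = 1.75, of which 35 × 0.025 = 0.875 favour the AI arm.

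**Step 4. Correlation**

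The document gives no correlations, so these are assumed. Simulation of 35 null comparisons with 25 per arm (6,000 runs each):

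| Between outcomes / between visits | Any | Favouring AI |
|---|---|---|
| 0 / 0.5 | 81% | 55% |
| 0.2 / 0.5 | 76% | 44% |
| 0.3 / 0.6 | 69% | 37% |
| 0.5 / 0.7 | 54% | 27% |

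**Step 5. One primary outcome or blanket correction**

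Bonferroni over 35 tests needs 0.05 / 35 = 0.0014 per test. For a standardised effect of 0.5 with 25 per arm, t-test power is then about 6.5%, against 41% for one test at 0.05. A single primary outcome is much the cheaper control in a trial of this size.

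**The case against.** The defence has good points.

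- **Depression is not a named aim.** A reader might infer that both adherence and depression are stated aims. Only adherence is. Depression comes in under mental health and as one of four example diagnoses, and the STAI, quality of life and the PSQI do bear on mental health or well-being. The missing depression scale is therefore a gap in covering the target population, not the loss of a declared endpoint.
- **Activity is recorded.** It would be wrong to say that Table 2 captures nothing about exercise, since EPIC-Norfolk and sedentary behaviour are there. They do not show whether a prescription was followed.
- **Adherence might be tracked elsewhere.** It would naturally be logged during treatment, and eligibility requires communication tools for remote monitoring (sections 2.4 and 2.5). The full protocol may say more. But the article presents Table 2 as comprehensive and never says that adherence is monitored, so the point holds for the schedule as published.
- **A chance benefit is not shown to be probable.** A reader might take 83% as the chance of a spurious benefit. It is the chance of any significant difference, including one against the AI arm. A false result favouring AI is more likely than not only if nearly all the per-visit tests are run and outcomes are uncorrelated or nearly so. With 19 to 20 tests, or with moderate correlation, it falls below one half.
- **Multiplicity detail can sit in an analysis plan.** This is accepted for adjustment of secondary outcomes. Naming the primary outcome belongs in the protocol, and this document itself sets 0.05 for all tests.

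**Conclusion.** The point stands in this form. Followed as published, the schedule cannot show whether AI prescriptions improve adherence to the prescribed exercise or depressive symptoms, and no outcome or visit is singled out to decide efficacy.

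The chance of at least one false positive is up to about 83% with 35 per-visit tests, and 62–64% with one longitudinal test per measure. For a false positive favouring the AI arm, the figures are up to about 59% and 38–40%. All assume independence. With the correlations assumed above, the 35-test figures fall to 54–81% and 27–55%. Even the lowest favourable figure, 27%, is roughly ten times the 2.5% of a single pre-specified test.

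The count depends on how Table 2 is read and on whether ANOVA replaces the per-visit tests, which section 4.5 leaves open. The absence of an adherence measure, a depression scale and a primary outcome does not depend on any of these assumptions.

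**What to change.** 1. Add the CES-D to Table 2 at baseline and at 6, 12 and 18 months. A baseline column is needed because the table has none.
2. Record prescribed and completed sessions in the AI arm, and recommended and completed sessions in the control arm, throughout the intervention period. The remote monitoring that eligibility already presupposes can carry this. State the length of that period once sections 2.1 and 4.2 are reconciled.
3. Name one mental-health scale at one visit as the single primary outcome, tested at two-sided 0.05. An example is the CES-D at the 6-month trial completion assessment, adjusted for baseline. If the sponsor prefers another scale, that one alone should be named, with its visit.
4. Label all other outcomes secondary or exploratory, report them with confidence intervals, and rest the efficacy claim on the primary only. Any adjustment among secondary outcomes can be left to the analysis plan.

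The cost is one 20-item form per visit, already in use in the project, a simple exercise log and a few sentences of protocol text. Fewer outcomes can then support a headline claim. This does not cure the limited power: with 25 per arm and an effect of 0.5, even a single primary outcome has about 41% by an unadjusted t-test.

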### Model inputs

3.1

In our study, a range of comprehensive assessment tools have been meticulously chosen to serve as inputs for the machine learning model (shown in Table 1). These include the State and Trait Anxiety Inventory (STAI), Center for Epidemiologic Studies Depression Scale (CES-D), Pittsburgh Sleep Quality Index (PSQI), and several others, each uniquely contributing to a multi-dimensional understanding of participant well-being. The collected data from these tools encompass various aspects of mental health, physical activity, social engagement, and general well-being. For instance, the STAI provides insights into anxiety levels, the CES-D focuses on symptoms of depression, while the PSQI assesses sleep quality. Other questionnaires like the CHAMPS Physical Activity Questionnaire and the Lubben Social Network Scale offer valuable data on physical activity habits and social network strengths, respectively. This diverse dataset is fed into the machine learning model to analyze patterns, correlations, and potential predictors of mental health outcomes.

**Table 1 tab1:** Comprehensive assessment tools utilized as input for machine learning model.

Questionnaires	Description
Mindfulness attention awareness scale (MAAS) (36)	This 12-item questionnaire focuses on assessing mindfulness during daily activities like conversation, commuting, and eating, underlining the importance of mental presence in everyday life
CHAMPS physical activity questionnaire for older adults (37)	A specialized 41-item questionnaire that gauges the weekly frequency and duration of physical activities particularly relevant to older adults
Sedentary behavior questionnaire (SBQ) (38)	This questionnaire specifically measures the time spent in nine different sedentary behaviors during a typical weekday and weekend, highlighting patterns of physical inactivity
Lubben social network scale – revised (LSNS-R) (39)	A 12-item questionnaire evaluating social engagement with family and friends, crucial for understanding social support networks
Social provisions scale (SPS) (40)	A 24-item scale that measures the availability and adequacy of social support in an individual’s life
UCLA Loneliness scale (41)	A 20-item scale focused on assessing feelings of loneliness and social isolation, reflecting on the emotional aspects of social health

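### The RCT schedules anxiety at two of its three visits and depression at none, so neither can be followed over the 6-, 12- and 18-month points that section 2.1 relies on

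*Protocol article*

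**What the plan says.** Section 2.1 (Study design) describes an assessment at trial completion and two follow-ups, and gives their purpose: "These assessments are designed to track and compare the short-term and long-term impacts of the AI-driven exercise prescriptions on the mental health outcomes". Section 4.3 (Outcome assessment and follow-up) dates them: "at 6 months (Trial Completion), 12 months (First Follow-up), and 18 months (Second Follow-up").

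Section 4.3 then assigns instruments to visits, in Table 2 and again in prose:

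- Anxiety: "The State and Trait Anxiety Inventory is administered at both the 6 months and 18 months follow-ups to assess changes in anxiety levels". The 12-month cell of the STAI row in Table 2 is empty.
- Depression: no row in Table 2 and no mention in the prose of section 4.3. The CES-D appears in section 3.1 as an input to the machine-learning model ("the CES-D focuses on symptoms of depression, while the PSQI assesses sleep quality") and in section 3.2, where physicians review it during annotation.
- Sleep, frailty and life space: the PSQI, FCI and "Life Space Questionnaire are administered at all three assessment points (6, 12, and 18 months) to monitor lifestyle changes and quality of life".
- Quality of life: "health-related quality of life and sedentary behavior are evaluated at all three time points". The instrument is not named.
- Memory: "subjective memory complaints are evaluated at the 12 months follow-up", and at no other visit.

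Section 4.5 (Statistical analysis) builds on the repeated visits: "Considering the multiple assessment points in our study, longitudinal data analysis techniques will be crucial". It names repeated measures ANOVA or mixed-model ANOVAs.

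**The concern.** The trial enrols people with depression, anxiety disorders, bipolar disorder or schizophrenia (section 2.4). A reader of section 2.1 would expect the core symptoms to be followed across the three assessments, yet the first follow-up visit carries neither an anxiety nor a depression scale, and depression is not scheduled as an RCT outcome at any visit.

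Two things are at stake. First, for anxiety, a benefit that has gone by month 12 cannot be told from one that fades gradually up to month 18. Second, a participant who attends at month 12 and then leaves contributes no anxiety reading after month 6, although they were seen. Readings that were not taken cannot be recovered later.

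**Working it through.** The plan states no figure to reproduce here. The check is a count of Table 2 against the prose of section 4.3, followed by what the schedule allows the analysis to see.

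**Step 1. Count of Table 2.** The table has 13 rows. Rows ticked: 12 at 6 months, 3 at 12 months, 7 at 18 months. The three rows at 12 months are subjective memory complaints; FCI, PSQI and life space; and quality of life with sedentary behaviour. Only the last two of these are ticked at all three visits.

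**Step 2. Mental-health and related measures by visit.**

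| Measure | 6 months | 12 months | 18 months | Visits |
|---|---|---|---|---|
| STAI (anxiety) | yes | no | yes | 2 of 3 |
| Depression scale | no | no | no | 0 of 3 |
| PSQI (sleep quality) | yes | yes | yes | 3 of 3 |
| Health-related quality of life | yes | yes | yes | 3 of 3 |
| Subjective memory complaints | no | yes | no | 1 of 3 |

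For the STAI, table and prose agree, so the empty cell is not an artefact of how the table was read.

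**Step 3. What two STAI occasions can show.** Let d6, d12 and d18 be the between-arm differences in STAI, and let D be the difference at month 6. Compare two courses:

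- Early loss: d6 = D, d12 = 0, d18 = 0.
- Gradual loss: d6 = D, d12 = D/2, d18 = 0.

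The schedule observes only d6 and d18. Both courses give (D, 0), so they cannot be told apart. In the ANOVA of section 4.5, time has 2 − 1 = 1 degree of freedom for the STAI, against 3 − 1 = 2 for the PSQI and quality of life.

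**Step 4. Loss between months 12 and 18.** Such a participant has one scheduled STAI reading, at month 6. The article gives no dropout rate. Purely as an assumption, take 10% to 20% lost in that interval. With the 50 participants of sections 2.1 and 4.1 this is 0.10 × 50 = 5 to 0.20 × 50 = 10 people. With the 40 stated in the Abstract it is 4 to 8. A 12-month STAI would give each of them a second reading.

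**Step 5. Depression.** The gap is not specific to month 12. Adding the STAI at 12 months alone would still leave depression unmeasured at all three visits.

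**The case against.** The strongest defence is that section 2.1 speaks of the assessments taken together. It does not promise every outcome at every visit. A reading at 6 months and another at 18 months does compare an earlier with a later effect on anxiety. With 3 of 13 rows ticked at 12 months, and table and prose in agreement, the light middle visit looks deliberate. Section 4.5 likewise does not promise three levels for each outcome. This largely stands: a lighter middle visit is not an error in itself, and two STAI occasions can be analysed. What remains is that section 2.1 offers all three assessments as tracking mental health outcomes, while the only anxiety or depression scale is absent from one of them. The defence has no answer on depression.

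A reader might infer more than the schedule supports:

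- That the 12-month visit holds nothing on mental health. It holds the PSQI, which Table 1 describes as covering sleep disturbance and daytime dysfunction; quality of life, where a mental domain can be neither confirmed nor excluded because the instrument is unnamed; and subjective memory complaints, which section 4.3 groups with the psychological assessments.
- That the trial cannot track mental health at all. It can compare anxiety between arms at two visits, and sleep and quality of life at three.
- That late dropouts give no symptom data after treatment. They are scheduled for the STAI at 6 months. Section 4.2 gives an intervention of 4 weeks while section 2.1 speaks of a 6-month trial period. Until those passages are reconciled, one cannot say whether month 6 is the end of treatment or already follow-up, nor that month 12 is where loss of benefit would first appear.
- That the STAI is the main outcome. The article names no primary outcome.

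The single reading of subjective memory complaints, at a visit without MoCA, MMSE or a memory test, is a minor side point. It still allows a between-arm comparison, and pairing it with an objective test is largely a preference.

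**Conclusion.** The concern holds in a limited form. The stated purpose of the three assessments and the schedule do not match: anxiety is measured at 2 of 3 visits and depression at 0 of 3. Neither can be followed over months 6, 12 and 18, although sleep quality and quality of life can, and anxiety can be compared between arms at 6 and 18 months.

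The counts rest on Table 2 and the prose of section 4.3, and need no assumption. The 5 to 10 people (4 to 8 if 40 are enrolled) whose only STAI reading would be at month 6 rest on an assumed 10% to 20% loss between months 12 and 18. This does not invalidate the trial. It is a cheap improvement that should be made before the 12-month visits take place.

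**What to change.** Preferred change:

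- Tick the STAI at 12 months in Table 2, using the same form as at 6 and 18 months, and amend the sentence on it in section 4.3.
- Add a CES-D row to Table 2, ticked at 6, 12 and 18 months, with a matching sentence in section 4.3. The scale is already in use as a model input.

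Cost: no new visits. By the item counts in Table 1 (STAI 40, CES-D 20), the extra load per participant is 40 + 20 = 60 self-report items at month 12 and 20 at each of months 6 and 18, or 60 + 20 + 20 = 100 items in all. The downside is this slightly greater questionnaire burden.

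If the present schedule is kept, restate section 2.1 so that anxiety is evaluated at 6 and 18 months only and depressive symptoms are not a trial outcome. That costs a sentence and adds no burden, but it narrows what the trial can claim.

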### Intervention measures

4.2

The 25 participants in the intervention group receive personalized exercise prescriptions generated by our AI model. These prescriptions are meticulously tailored based on each participant’s health profile and mental health status. The AI model determines the most suitable Type of Exercise for each individual, ranging from aerobic activities to strength training, depending on their physical and mental health needs. The Frequency of exercise is set, aiming for a balance that maximizes benefit while considering each individual’s lifestyle and capacity. Intensity levels are also customized, ensuring that exercises are challenging yet safe and achievable for each participant. Lastly, the Duration of each exercise session is specified by the AI model, optimizing the time spent on each activity for maximum efficacy. For example, for a participant with moderate depression and a sedentary lifestyle, the AI model might prescribe light aerobic activities like brisk walking or cycling for 30 min, three times a week. The intensity would be set at a moderate level, ensuring the participant can comfortably sustain the activity while gaining mental health benefits. The model may also suggest gentle yoga twice a week to improve flexibility and reduce stress, tailoring the duration to 20 min per session to match the participant’s initial physical fitness level. The intervention lasts for a period of 4 weeks, during which participants adhere to their personalized exercise regimen. The control group, comprising another set of 25 participants, receives standard care practices. This generally includes generic health advice and non-tailored exercise recommendations, reflecting the conventional approach to mental health management. The control group’s treatment does not involve the AI-driven customization of exercise parameters, serving as a baseline to evaluate the effectiveness of the personalized exercise prescriptions provided to the intervention group.

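### Lifetime-history questionnaires are scheduled only at the 6-month visit, among the outcomes, although such history is essentially fixed before randomisation

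*Protocol article*

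**What the plan says.** The protocol article, section 4.3 (Outcome assessment and follow-up), introduces the Table 2 schedule as one designed "to evaluate a broad spectrum of outcomes across different time intervals: at 6 months (Trial Completion), 12 months (First Follow-up), and 18 months (Second Follow-up". Under the lifestyle and quality-of-life heading it then states that "the study also incorporates the Reproductive, Florida Cognitive Activity Lifetime Stimulation, and Epic-Norfolk Physical Activity Questionnaire at the 6 months mark". The matching row of Table 2, "Reproductive, Florida cognitive activitylifetime stimulation, and epic-Norfolk physical activity questionnaire (34", carries a single tick, which the text places at 6 months. Nothing is planned for this row at 12 or 18 months.

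Section 2.1 (Study design) describes the 6-month visit as taking place "initially at the end of the 6 months trial period (Trial Completion Assessment", while section 4.2 (Intervention measures) says "The intervention lasts for a period of 4 weeks". Section 4.5 (Statistical analysis) plans that "comparative analyses between the intervention and control groups will be conducted using independent *t*-tests", with rank, chi-square or exact alternatives. It describes the purpose as "This will enable us to detect any significant differences arising from the intervention" and sets the threshold: "All statistical tests will be two-tailed, with a significance level set at *p* < 0.05".

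**The concern.** An outcome has to be something that the intervention could change. Cognitive activity accumulated over a lifetime is almost wholly determined before an adult enters the trial, and an exercise programme afterwards cannot alter it. The same holds for the Reproductive questionnaire if it records history. Placed among outcome assessments and followed by a general comparison of arms, these forms could yield a difference that is read as a treatment effect when it cannot be one.

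The timing also works against the legitimate use of such data. History is useful for describing the arms at entry and for covariate adjustment, and both uses call for a value on every randomised participant, obtained before allocation can colour recall. A form first given at 6 months provides neither.

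**Working it through.** The plan states no figure on this point, so the check is a comparison of sections with some supporting arithmetic.

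**Step 1: when are the forms collected?** The text of section 4.3 and Table 2 agree on 6 months only. Table 2 has no baseline column. Table 1 (model inputs, section 3.1) does not list either form. The article therefore shows no collection before randomisation.

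**Step 2: is that visit after the intervention?** Section 2.1 puts it at the end of a 6-month trial period, whereas section 4.2 gives an intervention of 4 weeks. These two statements need to be reconciled, but on either reading the visit follows both randomisation and the intervention.

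**Step 3: what role are the forms given?** Section 4.3 calls the contents of the schedule outcomes. Table 2 has a separate row for descriptors, and these forms are not in it. Section 4.5 exempts no variable from the between-arm comparison.

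**Step 4: what could a difference mean?** If the true effect is nil, three explanations remain: chance imbalance, differential dropout before 6 months, and differential recall after allocation.

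**Step 5: how large could the chance component be?** Inputs: 25 per arm (sections 2.1 and 4.1), two-sided alpha 0.05 (section 4.5), standardised effect size 0.5 (section 2.1).

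- One test at 0.05 gives a 5% chance of a false positive.
- Two tests, assuming independence and one score per form: 1 − 0.95² = 0.0975, or 9.75%.
- Standard error of a standardised difference: √(2/25) = 0.283.
- Chance that an unaffected variable differs by at least 0.5 in either direction: 0.5/0.283 = 1.77, which gives a two-sided normal tail probability of about 7.7%.
- Difference needed for p < 0.05: t(0.975, 48 df) × 0.283 ≈ 0.57.

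**Step 6: how much entry information is lost?** The article gives no dropout rate. Assuming 10–20% leave before 6 months, 0.10 × 50 = 5 to 0.20 × 50 = 10 participants have no history data. The abstract gives 40 participants instead of 50; on that figure the range is 4 to 8. Last observation carried forward, one of the missing-data methods named in section 4.5, cannot help because no earlier value exists. Multiple imputation is possible but is a poor substitute for asking at entry.

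**The case against.** The strongest case on the other side has four parts.

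**Content is inferred.** The article describes no items, scoring or recall period. The lifetime element is explicit only in the name of the Florida form, and the Reproductive form's historical content is a reading of its title. Either form might include some current items. This stands, and it is why the point about the Reproductive form is conditional.

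**No test of these forms is announced.** A reader might infer that the plan commits to reporting any difference on them as an intervention effect. The documents do not support that. No sentence singles out either form for a test. Their outcome role comes from the general introduction to Table 2 together with the general wording of section 4.5, which also plans descriptive summaries of participant characteristics and other relevant variables. A statistical analysis plan, not shown here, could keep the forms out of the outcome comparisons. That answers the testing half of the point but not the scheduling half, because no analysis plan can recover a history from someone who left before being asked.

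**Fixed history can be asked late.** If the value does not change, a 6-month answer is close to the entry value for those who stay. This is true for retained participants, subject to recall after allocation. It does nothing for those who leave.

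**The figures are unremarkable.** A reader might take 9.75% as an inflation peculiar to this design. It is the ordinary error of two independent 5% tests and would apply to any two measures without an effect. The dropout range is an assumption.

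It is also true that Table 2 has no baseline column for any instrument. That is a broader matter with a different remedy: measures that can respond to treatment would need an added baseline, whereas these two forms need to be moved.

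**Conclusion.** The point holds as a minor scheduling and labelling fault. The Florida lifetime cognitive-activity form, and the Reproductive form if it is historical, are collected only after the intervention and sit in a schedule of outcomes, although the history they record is essentially fixed before randomisation. A between-arm difference on them would not be evidence of an effect. The more durable harm is the loss of entry data for early leavers: 5 to 10 of 50 participants under an assumed 10–20% loss, with the actual rate unknown.

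The conclusion rests on the forms being what their names suggest and on there being no collection at entry beyond what the article shows. It does not extend to the Epic-Norfolk physical activity questionnaire in the same row, since physical activity can respond to an exercise programme. No primary endpoint, hypothesis or sample-size statement in the article depends on the two forms, so the trial's main conclusions are not at risk.

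**What to change.** Move the Reproductive and Florida lifetime cognitive-activity questionnaires out of the 6-month column and into the consent and screening session that section 2.2 already provides before randomisation. Leave the Epic-Norfolk questionnaire at 6 months, which means splitting the Table 2 row. Add one sentence to section 4.5 saying that the two history forms describe the arms at entry or serve as covariates and are not tested as outcomes. If the Reproductive form turns out to contain items on current status, say which items are treated as history.

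The cost is a slightly longer entry session, a split table row and one added sentence. No extra visit, staff or items are needed. The change has to be made before enrolment into the randomised phase to be of full use, because data from participants who leave early cannot be obtained afterwards.
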